## Abstract

•Multicenter trial for individualized volume de-escalation in oropharyngeal SCC.•Reduced elective CTV based on T-stage, lymphatic involvement, and lateralization.•No contralateral nodal irradiation for completely lateralized tumors.•Only irradiating LNL IV in case of LNL III involvement.•Sparing of LNLs I and V in many patients.

Multicenter trial for individualized volume de-escalation in oropharyngeal SCC.

Reduced elective CTV based on T-stage, lymphatic involvement, and lateralization.

No contralateral nodal irradiation for completely lateralized tumors.

Only irradiating LNL IV in case of LNL III involvement.

Sparing of LNLs I and V in many patients.

## Introduction

Curative intended treatment of squamous cell carcinoma (SCC) of the oropharynx can consist of surgery, (chemo)radiotherapy, or a combination of both. When treated with radiation, a large part of the lymphatic drainage system of the neck which is at risk of harboring occult metastases, is irradiated − the “elective clinical target volume (CTV)” [1], [2], [3]. The elective CTV is currently based on clinical recommendations, but there is only limited quantitative data available on (occult) lymphatic spread and the required size of the elective CTV [3], [4], [5], especially with regard to further personalization.

Elective irradiation of the neck lymph node levels (LNL) is associated with early and late toxicities, which potentially lead to hospitalization or long-term symptoms with subsequent life-quality impairment [6], [7], [8], [9], [10], [11]. In addition, there is increasing interest in possible immune-sparing effects of radiotherapy de-escalation. Irradiation of the lymph nodes and lymph drainage system is associated with the development of lymphopenia [12]. By volume de-escalation, the lymphatic system could be spared more, potentially leading to improved antigen-priming, less lymphopenia and better survival outcomes [13], [14], [15], [16], [17].

Several observations suggest that there is potential for safely reducing the elective CTV without substantially increasing the risk of regional failure. There is low incidence of treatment failure and out-of-field lymph node metastases after standard-of-care (chemo)radiotherapy in oropharyngeal SCC. Leeman et al. showed a local treatment failure at 5 years of 4.2%, with 2.9% regional nodal failure and no marginal or isolated out-of-radiation-field failure [18]. Similar results were found by Van den Bosch et al., who found a 2-year recurrence rate in electively irradiated lymph node regions of 5.2% [19]. Several trials applying reduced elective CTVs have reported low rates of N-site recurrences in unirradiated levels. This includes studies on unilateral neck irradiation for lateralized tumors [20], [21], [22] as well as the EVADER trial [23]. Many de-escalation studies have focused on HPV-positive tumors because of the favorable prognosis or found better results for the patients with HPV-positive tumors when de-escalating treatment [23], [24], [25], [26], [27], [28].

We developed a statistical model to estimate the patients’ individual risk of occult lymph node metastases in clinically negative LNLs in newly diagnosed oropharyngeal SCC patients, based on the patient’s location of clinically detected metastases, T-stage, and lateralization of the primary tumor [29], [30], [31], [32]. The elective CTV is subsequently defined based on a patient’s individualized risk such that the overall risk of occult lymph node metastases in all non-irradiated LNLs (out-of-field) is estimated to be below 10%. This leads to substantially smaller elective CTVs compared to current guidelines [3].

The aim of this phase II clinical trial is to determine the efficacy and safety of the use of a personalized volume de-escalated elective nodal CTV in oropharyngeal SCC patients treated with primary (chemo)radiotherapy.

### Previous work leading to the trial design

We collected a multi-institutional dataset of 598 oropharyngeal SCC patients in whom the detailed patterns of lymph node involvement are reported. For each patient, lymph node involvement was recorded for each individual LNL based on the available diagnostic modality. Pathology results after neck dissection was reported for the subset of surgically treated patients. In addition, primary tumor location, lateralization, HPV-status, and T-stage is reported among other patient and tumor characteristics. The dataset is publicly available [33], [34], [35]. The publicly available online platform LyProX.org was developed to visualize published datasets in an intuitive and interactive manner.

To define the elective nodal CTV, we are interested in the conditional probability that a clinically negative LNL harbors occult metastases, given the primary tumor characteristics and the location of clinically detected lymph node metastases. This conditional probability of occult disease depends on 1) the probability of the tumor to spread to the LNL of interest, and 2) the sensitivity and specificity of clinical diagnostic methods. To combine both aspects, we developed a comprehensive statistical model to predict the probability of occult disease per LNL using a Hidden Markov model (HMM). In this model, the state of involvement of a LNL is described by a latent binary random variable, which indicates if the LNL is healthy or harbors metastases (including occult metastases). The state of lymph node involvement of a patient is then described by a vector of binary random variables. Each LNL is further associated with an observed state, another binary random variable that indicates if a LNL is clinically diagnosed as involved. The HMM is used to describe the spread from the primary tumor to the LNLs and progression from an involved LNL to a downstream LNL. The model is parameterized using a directed graph where the arcs represent the possible spread to and between LNLs, resembling the anatomically defined lymph drainage of the neck. The main model parameters are the probabilities of spread associated with each arc. The latent true state of involvement and the clinically observed involvement are linked via sensitivity and specificity of imaging. Thus, we can compute the likelihood of the observed dataset of 598 patients given the model parameters. We use Markov Chain Monte Carlo (MCMC) sampling to draw these parameters from the posterior distribution, comprised of the likelihood and a uniform prior. This approach naturally provides uncertainty bounds for the model's parameters and consequently also for the predicted risk of occult involvement. Model training is performed based on a consensus decision on the most likely state of involvement given all diagnostic modalities available for each patient and LNL in the dataset, which is assumed to represent the true latent state of involvement. Sensitivities and specificities are not learned, but taken from literature values, originating from the comparison of clinical and pathological involvement of patients receiving neck dissection. For risk calculations we set specificity to 1 and sensitivity to 0.81. This corresponds to the literature values for sensitivity of CT and MRI reported by De Bondt et al. [36]. A specificity of 1 corresponds to the assumption that clinically involved LNLs truly harbor metastases and do not represent false positives. A detailed description of the methodology can be found in the respective publications [29], [30], [31], [37]. The model presented in [31] is representative for the model underlying the design of the DeEscO trial, despite not being identical in all details.

The trained model can then be used for predicting the probability of occult involvement per LNL for individual patients. The patient characteristics that are input to the model are 1) clinical involvement per LNL, 2) early (T1/T2) versus advanced (T3/T4) T-stage, and 3) lateralization of the primary tumor. In addition, we considered central tumors, where there is no clear origin of the primary tumor lateral to the midline. For the common states of the primary tumor and clinical lymph node involvement (the patients that occurred at least once in the dataset), the model was used to predict the risk of occult disease in the clinically negative LNLs. To define the elective nodal CTV (referred to as CTV-3 below), the clinically negative LNLs are ranked according to their risk of occult involvement. The LNLs with the highest risk are included in the CTV-3 until the cumulative risk of involvement in all remaining LNLs is below 10% for 95% of the model parameter samples generated through MCMC. As a final measure of quality assurance, the CTV-3s constructed in this way have been discussed individually by the investigators, to ensure consistency with data and clinical judgement and experience (Table 1, Supplementary Tables 1–5).

**Table 1 t0005:** General rules.

**General rules**	
**1**	Include all involved lymph node levels (LNLs) in the CTV-3.
**2**	Ipsilateral level II (including IIa and IIb) is always irradiated.
**3**	Level Ia is never included in the CTV-3 unless clinically involved. In case of involvement of level Ia, the study PI at USZ must be contacted for a treatment decision.
**4**	If level IV is involved, the entire level (both IVa and IVb) is included in the CTV-3. If level IV is not involved, level IVb is never included in the CTV-3.
**5**	If level V is irradiated according to Supplementary Tables 1–5, levels Va and Vb are irradiated. Level Vc is irradiated if level Vb is involved.
**6**	Level VII is never included in the CTV-3 unless clinically involved. In case of level VIIa involvement, both level VIIa and VIIb are included in the CTV-3. In case of level VIIb involvement, only level VIIb (not VIIa) is included in the CTV-3.
**7**	If a level that is not irradiated according to Supplementary Tables 1–5 but partially overlaps with PTV-1, PTV-2, or PTV-3, then only the overlapping part of the level will be irradiated as part of the respective PTV. The non-overlapping part is not to be included in the CTV-3.

The supplementary tables cover the most commonly observed cases in our database (85% of the cases in our database) and a select number of plausible cases. The investigators at University Hospital Zurich have a table with all (theoretically) possible cases and their treatment recommendations available.

## Design

### Treatment description

The DeEscO study will be conducted as a prospective, multicenter, open label, single-arm trial at six centers in Switzerland (University Hospital Zurich, Bern University Hospital, University Hospital Geneva, Cantonal Hospital Aarau, Cantonal Hospital Bellinzona, and Réseau Hospitalier Neuchâtelois).

The study aims to recruit 120 oropharyngeal SCC patients treated with definitive (chemo)radiotherapy with curative intent.

The study includes patients with newly diagnosed (no pre-treatment) SCC of the oropharynx (ICD-10 codes C01, C09, C10), T1-4, N0-3, irrespective of p16-status. Treatment with definitive (chemo)radiotherapy is planned, including elective irradiation of the cervical lymph nodes. Patients need to have an ECOG performance score ≤ 2, have a consultation with physical examination by a head and neck surgeon, radiation oncologist or medical oncologist within 30 days prior to registration and patients should have received staging with FDG-PET/CT prior to registration. In case of inability to perform or contra-indications, at least a contrast-enhanced MRI is obligatory.

Patients are excluded in case the tumor extends from the oropharynx into other levels, such as the oral cavity, naso- or hypopharynx, or if patients are diagnosed with distant metastases. Previous surgery, chemotherapy or radiotherapy treatment in the head and neck area is not allowed, except for singular lymph node dissections for diagnostic purposes or treatment of Tis-T2 glottic laryngeal carcinoma without treatment of the lymphatic drainage area.

Patients will receive treatment with definitive radiotherapy and if indicated, standard-of-care chemotherapy. Dose prescription and treatment of the primary tumor is performed according to standard-of-care. The study-specific intervention is the personalized definition of the elective CTV as described below.

Radiation volumes and doses are based on Nutting et al. (Lancet Oncology, 2023) [38] and the DAHANCA 2020 guidelines [39].

The radiotherapy volumes will be defined as follows:•GTV-T: Macroscopic gross tumor in T site•GTV-N: Macroscopic tumor in N site(s)•CTV-1: 5 mm expansion of the combined GTV (GTV-T and GTV-N), corrected for anatomical barriers.•CTV-2: 10 mm expansion of the combined GTV, corrected for anatomical barriers.•CTV-3: Defined as the elective target volume. LNLs are to be delineated according to Grégoire et al. [1] The LNLs to include in the CTV-3 are defined in Tables 1 and Supplementary Tables 1–5.•For expansion from CTV to PTV, an expansion of 3–5 mm – to the discretion of the participating center – is used. All PTVs should be cropped to the skin.

### Radiotherapy doses

The following physical radiotherapy doses will be applied to the target volumes:•CTV-1/PTV-1: 65–70 Gy•Optional: CTV-2/PTV-2: 60–66 Gy•CTV-3/PTV-3: 50–56 Gy

Radiotherapy will be given as simultaneous integrated boost (SIB) in 30–35 fractions of 1.8–2.2 Gy (in CTV-1 and CTV-2) and 1.47–1.8 Gy (in CTV-3) over 6–7 weeks – to discretion of the treating participating center. PTV-1 and PTV-2 may receive the same radiotherapy dose (as described e.g. in Nutting et al. – in this case there would be no “intermediate dose”/“intermediate risk volume”), or the PTV-2 can be omitted, if a 10 mm expansion of the GTV is included in the target volume CTV-3.

### Personalized elective nodal CTV de-escalation

The elective treatment volume (CTV-3) will be personalized based on T-stage, midline extension and clinically involved levels according to Tables 1 and Supplementary Tables 1–5. Table 2 and Fig. 1 A-F provide examples of common de-escalation scenarios.

**Table 2 t0010:** Treatment recommendations for the most common presentations.

				**To be included in CTV-N**	**To be included in CTV-N**
**T-stage**	**Midline extension**	**Nodal involvement ipsilateral**	**Nodal involvement contralateral**	**Ipsilateral neck**	**Contralateral neck**
T1-4	FALSE	II	−	II, III	−
T1-4	TRUE	II	−	II, III	II
T1-2	FALSE	−	−	II	−
T3-4	FALSE	−	−	II, III	−
T1-2	TRUE	−	−	II	II
T3-4	TRUE	−	−	II, III	II
T1-4	FALSE	II, III	−	II, III, IVa	−
T1-4	TRUE	II, III	−	II, III, IVa	II
T1-2	TRUE	II	II	II, III	II, III
T3-4	TRUE	II	II	(Ib)*, II, III	II, III
T1-4	TRUE	II, III	II	II, III, IVa	II, III
T1-4	TRUE	II, III, IV	II	II, III, IV, V^**^	II, III
T1-4	FALSE	II, III	II	(Ib)*, II, III, IVa	II, III

*Only irradiate level IB electively if level IIA on the same side is involved.

**Level Va and Vb are irradiated.

**Fig. 1 f0005:**
[figure not shown]
**A-F. Schematic examples of the personalized elective nodal CTV de-escalation.** Schematic examples of the personalized elective nodal clinical target volume (CTV) de-escalation. Green illustrates unirradiated lymph node levels (LNLs), yellow illustrates irradiated LNLs (part of the elective CTV), red illustrates LNLs with macroscopic lymph node metastases. **Fig. 1A** shows a situation where a patient is diagnosed with a T1/T2-stage tumor that does not cross the midline, without any lymph node metastases. In this case, in the trial only ipsilateral level II will be irradiated. **Fig. 1B** shows a patient diagnosed with a T3/T4-stage tumor that crosses the midline, without any lymph node metastases. In this case, LNLs II and III on the ipsilateral side and level II on the contralateral side will be irradiated. **Fig. 1C** shows a patient with a lateralized T1/T2-tumor and macroscopic lymph node metastases in ipsilateral level II. Here, LNLs II and III on the ipsilateral side will be irradiated, no levels on the contralateral side will be irradiated. **Fig. 1D** shows a patient with a T3/T4-tumor with midline extension and macroscopic lymph node metastases in ipsilateral level II. In this case, LNLs II and III on the ipsilateral side and level II on the contralateral side will be irradiated. **Fig. 1E** shows a patient with a T3/T4-tumor, with midline extension, and macroscopic lymph node metastases in ipsilateral levels II and III and contralateral level II. In this case, levels Ib-IVa on the ipsilateral side and levels II and III on the contralateral side will be irradiated. **Fig. 1F** shows a T3/T4-tumor with midline extension diagnosed with macroscopic lymph node metastases in ipsilateral levels II, III and IVa and contralateral level II. Here, ipsilateral levels II-V and contralateral levels II and III will be irradiated. (For interpretation of the references to colour in this figure legend, the reader is referred to the web version of this article.)

Early T-stage is defined as T-stages 1–2 and advanced T-stage as T-stages 3–4. Midline extension is defined as a patient in whom any part of the primary tumor GTV extends beyond the midsagittal plane. Central tumors are those with similar tumor extension on both sides of the midsagittal plane by the judgement of the treating physician. Tumors extending on both sides but with the main tumor mass located on one side are instead classified as “lateralized tumors with midline extension”.

For defining clinical lymph node involvement, nodes with an uptake > 3 SUV or size > 1.5 cm or central necrosis on FDG-PET/CT are to be considered clinically involved unless confirmed negative through fine needle aspiration (FNA). In case of ambiguity after radiological work-up regarding lymph node involvement, FNA is recommended. We recommend FNA control of all ambiguous nodes > 1 cm, regardless of the SUV. For the definition of clinical lymph node involvement per level, in case of a lymph node conglomerate or large nodes extending over 2 levels, both levels should be considered as involved.

### Follow-up

During the treatment, there will be weekly clinical visits to evaluate toxicities. The first clinical assessment will take place 6–8 weeks after finishing treatment. An ultrasound examination of the neck LNLs is strongly recommended. Only nodes > 1 cm outside of the irradiated volume should be cytologically controlled with FNA within the first 4 months.

The first follow-up PET/T scan will take place 3–4 months after finishing treatment. Afterwards, follow-up visits will take place every 3 months during the first 2 years of follow-up, including assessment of toxicities and imaging if needed. If no imaging is performed, an ultrasound examination is mandatory to rule out lymph node recurrences/progression. Further standard follow-up PET/CT scans will take place 9–10 months and 2 years after finishing treatment. During the third year of follow-up, follow-up visits will take place every 6 months. If no imaging is performed, an ultrasound examination of the neck is mandatory.

### Endpoints

The primary endpoint is the rate of out-of-field N-site recurrences 2 years after the end of the primary (chemo)radiotherapy treatment. An event towards the primary endpoint is defined as any N-site recurrence in non-irradiated LNLs.

Secondary endpoints include the rate of out-of-field N-site recurrences 3 years after the end of the primary (chemo)radiotherapy treatment (in direct analogy to the primary endpoint), loco-regional control, progression-free survival and overall survival. For patients with recurrence, we will analyze detailed patterns of failure in terms of time to event and location of the recurrence, distinguishing T-site recurrence, N-site recurrence or persistence of grossly involved lymph nodes, isolated N-site recurrences in electively treated LNLs, and isolated recurrences in unirradiated LNLs. In addition, we will analyze early (≤3 months after treatment) and late (>3 months after treatment) toxicities of treatment: assessed by grading of toxicities according to CTCAE v5 [40]. Assessment of toxicities will be performed weekly (1x/week) during radiotherapy and during every follow-up visit. Overall toxicity will be evaluated according to the TAME methodology [41]. Other secondary endpoints include blood examination, including full blood count with lymphocytes taken during routine examination before and after the last radiotherapy, and quality of life (QoL) assessed using the EORTC QLQ C30 and Head and Neck Module HN43 questionnaires at the start of treatment, as well as after completing treatment, and 6, 12 and 24 months after radiotherapy [42], [43]. The evaluation of dysphagia using the M.D. Anderson Dysphagia Inventory (MDADI) [44] at 12 and 24 months is a planned addition.

Tumour response on imaging is assessed according to the RECIST criteria. Persistence is defined as progressive disease (PD), stable disease (SD) or incomplete response of the primary tumour (local persistence/persistence of the primary tumour) or nodal metastases at baseline (nodal persistence). Recurrence is defined as new pathological lesions/disease (new lesions or new lesions after complete response before) of the primary tumour (local recurrence), previous pathological lymph nodes (known lymph nodes), new lymph nodes, or distant metastases.

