### Statistical analyses

The primary endpoint will be evaluated according to the per-protocol treatment, although all primary analyses will follow both the per-protocol and intention-to-treat principles.

The primary endpoint “Out-of-field lymph node recurrence” will be reported as the Kaplan-Meier estimator for the time-to-event at 2 years. The calculation of the Kaplan-Meier estimator at 2 years will include the events detected at the 24-months follow-up visit (which may occur at 2 years +/- 1 month). Patients lost to follow-up and patients who die due to any cause are right-censored.

In addition to the overall rate of Out-of-field lymph node recurrences, we will analyze whether 1) Out-of-field lymph node recurrence was the initial cause for loco-regional failure, or whether 2) recurrence/persistence of the primary tumor or grossly involved lymph nodes present at baseline was observed simultaneously or prior to the Out-of-field lymph node recurrence. In case 1, irradiating the respective LNL electively may have prevented loco-regional failure. In case 2, loco-regional failure may have occurred irrespective of volume-de-escalation, and the Out-of-field lymph node recurrence may be due to lymphatic spread of the recurrent/persistent tumor. To determine the rate of “Out-of-field lymph node recurrences being the initial cause for loco-regional failure”, we will perform Kaplan-Meier analysis where patients with recurrence/persistence of the primary tumor or grossly involved lymph nodes present at baseline are right-censored.

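### Persistence is any RECIST response short of complete, not tied to the scheduled PET/CT or to viable disease, so a size-only residual censors the patient from the initial-cause analysis and moves a later out-of-field recurrence to case 2

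*Protocol article*

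**What the plan says.** In the protocol article, Endpoints sets the scale: "Tumour response on imaging is assessed according to the RECIST criteria". The definition follows: "Persistence is defined as progressive disease (PD), stable disease (SD) or incomplete response of the primary tumour". It extends to the neck with the words "or nodal metastases at baseline (nodal persistence". Everything short of complete response is therefore persistence, in the primary tumour or in baseline nodes. The definition mentions no assessment time, uptake or cytology.

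Statistical analyses uses the term twice.
- It splits out-of-field recurrences. Case 1 is an out-of-field recurrence that started the loco-regional failure. Case 2 is one seen together with, or after, recurrence or persistence at the primary tumour or baseline nodes. Of the latter it says: "In case 2, loco-regional failure may have occurred irrespective of volume-de-escalation".
- For the rate of case 1 it says: "we will perform Kaplan-Meier analysis where patients with recurrence/persistence of the primary tumor or grossly involved lymph nodes present at baseline are right-censored".

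Follow-up schedules imaging that could inform the definition. The first follow-up PET/CT "scan will take place 3–4 months after finishing treatment", and "Further standard follow-up PET/CT scans will take place 9–10 months and 2 years after finishing treatment". Neither is linked to persistence. The post-treatment cytology rule in that section covers only nodes outside the irradiated volume, so it does not settle the status of treated baseline nodes.

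**The concern.** The case 1/case 2 split separates failures that elective irradiation of the omitted level might have prevented from those that would have happened anyway. It is the most direct reading of whether volume reduction caused harm, and a single-arm trial has no control group against which to check it.

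The split works only if persistence means tumour that is still active. As printed, it also takes in a node that has shrunk, shows no uptake, and is stable or on its way to resolving. If such a patient later recurs only in an unirradiated level, that is the event case 1 is meant to count. The printed rule places it in case 2 and censors the patient in the corresponding Kaplan-Meier analysis.

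**Working it through.** **1. Following the rules for one patient.** Suppose a baseline node measures 4 cm, is 1.6 cm without uptake at the 3–4-month PET/CT, and an isolated recurrence later appears in an unirradiated level.
- Endpoints: the node has not responded completely, so it is nodal persistence. This takes RECIST as a size-based scale; the article gives no version or thresholds.
- Statistical analyses: persistence was observed before the out-of-field recurrence, so the event is case 2 and the patient is right-censored in the initial-cause analysis.
- Primary endpoint: any recurrence in a non-irradiated level counts, so the event is still counted there.

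If incomplete response is read as complete response never having been reached, a node that resolves by the 9–10-month scan escapes the label. A node that stays stable without uptake does not.

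**2. The plan's own figure.** Inputs from Sample size calculation: S = 0.9 at 2 years, 90% interval, log-minus-log transformation, n = 104.
- SE = sqrt((1 − S)/(nS)) / |ln S| = sqrt(0.1/(104 × 0.9)) / 0.10536 = 0.3102
- Limits = S^exp(±1.645 × SE) = 0.839 and 0.939; width 0.0997
- n = 103 gives 0.1002, so 104 is the smallest n with width at most 0.10. 104/(1 − 0.13) = 119.5, rounded up to 120.

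Both stated figures reproduce and are not in dispute.

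**3. Illustration of the effect.** Assumptions, not in the documents: a fraction f of 104 patients is right-censored as persistent at 3.5 months; the out-of-field rate is 10% at 2 years with constant hazard λ = −ln(0.9)/24 per month; without this censoring all these events would be case 1.
- Variance term: V = (e^(3.5λ) − 1)/104 + (e^(24λ) − e^(3.5λ))/(104(1 − f)), with e^(3.5λ) = 1.0155 and e^(24λ) = 1.1111. SE = sqrt(V)/|ln 0.9|; limits as in step 2.
- Events kept: 104(1 − e^(−3.5λ)) + 104(1 − f)(e^(−3.5λ) − 0.9).
- Example, f = 0.4: V = 0.000149 + 0.001532 = 0.001681; SE = 0.389; limits 0.819 and 0.946; width 0.127. Events = 1.59 + 5.29 = 6.9.

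The last two columns let censored patients have 2 or 3 times the out-of-field rate of the others, with the overall rate held at 10%. Example, f = 20%, ratio 2: others 0.10/(0.8 + 0.2 × 2) = 8.3%, censored 16.7%. After month 3.5 only the others contribute, and the Kaplan-Meier estimate is 8.6%.

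| f | Patients censored | Events kept | 90% CI width | Rate read, equal risk | Ratio 2 | Ratio 3 |
|---|---|---|---|---|---|---|
| 0 | 0 | 10.4 | 0.100 | 10% | – | – |
| 10% | 10.4 | 9.5 | 0.105 | 10% | 9.2% | 8.6% |
| 20% | 20.8 | 8.6 | 0.111 | 10% | 8.6% | 7.6% |
| 30% | 31.2 | 7.8 | 0.118 | 10% | 8.0% | 6.8% |
| 40% | 41.6 | 6.9 | 0.127 | 10% | 7.6% | 6.2% |

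With equal risk, the case 1 count falls by 0.9 (10.4 − 9.5) to 3.5 (10.4 − 6.9) events, while the estimated rate does not move.

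**The case against.** The case on the other side is substantial, and much of it stands.

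- **Bias.** A reader might infer that the rule makes volume reduction look safer. If the nodes are controlled and these patients have the same out-of-field risk as the rest, the censoring is non-informative and the Kaplan-Meier rate stays at 10% in expectation. Nothing in the document says their risk is higher. What remains is lost precision and a lower case 1 count.
- **Loco-regional control and progression-free survival.** A reader might infer false failures in both. The article names these endpoints without defining their events, so they are affected only if persistence counts as an event there. The patterns-of-failure analysis is introduced for patients with recurrence, so a patient with only a shrinking node does not clearly enter it.
- **Early labelling.** Follow-up says "The first clinical assessment will take place 6–8 weeks after finishing treatment", with ultrasound strongly recommended. One might infer that persistence can be declared then. No sentence says that response is classified at that visit.
- **The trial's own node criteria.** The baseline rule, under Personalized elective nodal CTV de-escalation, accepts size above 1.5 cm alone as involvement unless cytology is negative. The 1.6 cm node would meet it. Those criteria therefore do not contradict the persistence rule and cannot be borrowed unchanged.
- **Detail left elsewhere.** The RECIST version, assessment time and censoring date may be in the full protocol. This does not dispose of the point: the article prints a finished rule that counts every incomplete response, and uses it for censoring and attribution.

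**Conclusion.** The point holds for the supplementary analysis. Because persistence is any RECIST response short of complete, with no link to the scheduled PET/CT or to viable disease, a size-only residual without uptake is handled as a failure at baseline sites, and a true out-of-field first failure in that patient is lost from case 1.

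The primary endpoint and the sample size are unaffected. The size of the effect rests on an assumed 10–40% censored at 3.5 months and a 10% out-of-field rate: 0.9 to 3.5 fewer case 1 events of 10.4, and an interval width of 0.105–0.127 instead of 0.100. A downward-biased rate (9.2% to 6.2% in place of 10%) needs the further assumption of a two- to threefold higher out-of-field risk in the censored patients, which the documents do not support. No figure for loco-regional control or progression-free survival can be derived from the article.

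**What to change.** For endpoint coding only, with no change to patient care:
- Classify persistence from the 3–4-month PET/CT or later.
- Require residual uptake, positive cytology or histology where obtained, or progression on later scheduled imaging.
- State explicitly that this departs from the size-alone criterion used for baseline involvement.
- Do not censor, or assign to case 2, patients whose residual is size-only and resolves or stays stable without uptake.
- Date confirmed persistence to the first positive assessment.
- State whether persistence counts as an event for loco-regional control and progression-free survival.
- Report the initial-cause analysis under the printed RECIST definition as a sensitivity analysis.

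The cost is endpoint wording and one case report form field; all the scans are already scheduled. Recruitment is expected to end in January 2027, so the change can be made before the 2-year outcomes are complete. The downside is that some cases can be classified only at the 9–10-month scan.
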